## Abstract

**Background:**

Constipation is a common complication after stroke that can severely influence a patient’s quality of life and rehabilitation. Treatments for constipation after stroke vary. Acupuncture may improve spontaneous bowel movements, quality of life, and clinical symptoms. The study seeks to assess the preliminary effects of acupuncture on constipation after an ischemic stroke.

**Methods/design:**

This is a prospective randomized controlled pilot trial design in which 120 eligible patients will be randomly allocated to one of three groups. The acupuncture group (*n* = 40) will receive acupuncture and routine care, the medication group (*n* = 40) will receive mosapride citrate and routine care, and the control group (*n* = 40) will receive only routine care for ischemic stroke. Patients will be recruited 2 weeks to 6 months after stroke onset and will receive the intervention continuously over 4 weeks, with a follow-up period of 4 additional weeks. Adverse events will be recorded to assess the safety and tolerability of acupuncture for constipation after an ischemic stroke. The primary outcome will be the change in the weekly mean number of complete spontaneous bowel movements. Secondary outcomes will include any change in the weekly mean number of spontaneous bowel movements, mean stool consistency scores, mean straining scores during defecation, and frequency of laxative use. All outcome measures will be assessed at inception, after the intervention (4 weeks), and at the follow-up (8 weeks).

**Discussion:**

This study will provide evidence of the preliminary effects and inform future sample size calculations for studies of acupuncture for constipation following an ischemic stroke. These findings will inform subsequent large-scale randomized controlled trials.

**Trial registration:**

ISRCTN, 22214747. Registered on 17 August 2015.

**Electronic supplementary material:**

The online version of this article (10.1186/s13063-018-2750-0) contains supplementary material, which is available to authorized users.

## Background

Globally, stroke is the second leading cause of mortality and disability among adults over 60 years old [1, 2]. Due to an aging population, dietary changes, pronounced work-related stress, and rapid economic development, there is an increasing prevalence of stroke among younger individuals [3]. Constipation is a common complication after stroke [4]. Population-based studies indicate that approximately 30% to 60% of stroke patients suffer, or have suffered, from constipation following stroke [5–8]. This wide range can likely be attributed to the adoption of different time points [5, 7, 8], the diagnostic criteria used to measure constipation [4, 5] and patient characteristics [5, 6]. Constipation can severely impair a patient’s quality of life and rehabilitation [9]. Consequently, constipation incurs a heavy burden on patients, patients’ families, and society as a whole [10].

Treatments for constipation after stroke vary and include lifestyle changes [11–13], diet changes [14–18], use of laxatives, enemas, prokinetic drugs, and surgically implanted neuro-modulation [19]. Unfortunately, many of these treatments are poorly tolerated or rejected, or there may be a lack of clinical evidence supporting their use. Thus, there is a need for a safe, effective, and non-toxic therapy for constipation after a stroke.

Acupuncture has a history of more than 2000 years in China and plays an important role in traditional Chinese medicine [20]. A recent systematic review indicated that acupuncture is safe and tolerable, and may improve weekly spontaneous bowel movements (SBMs), quality of life, and constipation symptoms [21]. Acupuncture may, therefore, be an effective treatment for post-stroke constipation and it has several advantages compared with other therapies [22]. However, using acupuncture to treat constipation has not been validated with high-quality clinical evidence. In addition, clinical research focusing on acupuncture for constipation after stroke is rare [19]. Therefore, we designed this trial to assess the preliminary effects and inform future sample size calculations for studies of acupuncture for constipation following an ischemic stroke. Our hypothesis is that the effectiveness of acupuncture is no less than that of mosapride and better than routine health care.

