### Randomization and allocation concealment

Participants will be randomly assigned to one of three groups (the acupuncture group, the medication group, or the control group) using a 1:1:1 ratio. The generation and allocation of a random sequence for group assignment will be conducted by the Research Centre of Clinical Epidemiology, which is affiliated to Peking University Third Hospital in China. Individuals involved in participant randomization will be blinded and will not participate in the recruitment and inclusion of participants. The block randomization method (block size of 6) will be adopted to generate the random sequence, using the Statistical Analysis System (V.9.1.3; SAS Institute Inc., Cary, North Carolina, USA). Opaque computer-generated sealed envelopes will be produced for the randomization and allocation. The envelopes will be numbered consecutively with a serial number on the outside and will contain the allocation information. An envelope will be opened when a participant enters the study after the baseline measurements have been taken. Participants will be allocated to one of the three groups and receive an intervention according to their group allocation. The random allocation sequence and the opaque sealed envelopes will be kept separately by two specific researchers.

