#### Sample size

Since there are no previous three-armed randomized controlled trials that investigate this topic, the present study will provide effect size data for sample size calculations of subsequent large-scale randomized controlled trials. For practical reasons, a sample size of 40 per group and a total number of 120 participants will be recruited during the entire study according to outpatient and inpatient censuses of the hospital.

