### Outcome measures

#### Primary outcome measure

The primary outcome measure will be the change in the weekly mean number of CSBMs over the 4 weeks of the intervention and the 4 weeks of the follow-up. A CSBM is defined as a SBM unrelated to the administration of laxatives or finger manipulation, accompanied by a self-reported feeling of complete evacuation. Bowel movements achieved with the help of glycerin, enemas, or finger manipulation are not considered spontaneous. If bowel movements occur within 24 h after the intake of laxatives, they will not be considered spontaneous. However, if bowel movements occur more than 24 h after administration of laxatives, they will be considered spontaneous. The total number of CSBMs during the treatment period and follow-up period will be averaged to obtain mean weekly CSBMs.

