### Statistical analysis

The analysis of the primary outcome will be based on both a full analysis (intention-to-treat analysis) and per-protocol sets (per-protocol analysis). The analyses of secondary outcomes will be based on the per-protocol sets. The full analysis set refer to the participants who are randomized and receive at least one treatment session. Any missing data will be replaced by the last measured value. The per-protocol sets will be defined as the participants who receive all treatment sessions and completed the study according to the protocol.

The statistical analysis will be performed by a statistician who is blinded to participant group allocation and will not be involved in other aspects of the study. The SPSS statistical package (version 18.0, International Business Machines Corporation, China) will be used to analyze the data. All data will be kept in duplicate by specific researchers. The results of the quantitative data analyses will be presented as means ± standard deviation. The Kolmogorov–Smirnov test will be applied as the normality test for quantitative variables. The Wilcoxon test or analysis of variance (ANOVA) will be used to compare the difference between groups according to the results of the Kolmogorov–Smirnov test. The results for categorical data will be compared with the chi-squared test and presented as a percentage. The statistical significance level will be set at 0.05 (two-sided) with a 95% confidence interval.

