The objective of this study is to determine the preliminary effects of acupuncture on constipation after an ischemic stroke. The selection of a control group was a major issue in planning the design of the trial. Reported clinical trials of acupuncture for constipation after a stroke are scarce in both English and Chinese research databases. Consequently, we decided to pursue a pragmatic study design. Due to the scarcity of evidence supporting the use of acupuncture for constipation after a stroke, we did not include a sham acupuncture control group. However, if acupuncture proves to be effective in this study, we will then compare acupuncture with a sham treatment as the next step in clarifying the specific effects of acupuncture. Mosapride, a kind of serotonin 5-hydroxytryptamine 4 (5-HT_4_) receptor agonist, was designated as the positive drug control in the trial. Clinical evidence and guidelines indicate that 5-HT_4_ receptor agonists, such as prucalopride and mosapride, improve the mobility of the gastrointestinal tract and are effective in the management of constipation [39–44]. Since prucalopride is not widely applied in clinical practice in Beijing, we chose mosapride citrate as the drug of choice for the medication group [45, 46].

The study is a prospective randomized controlled pilot trial. Randomization and allocation concealment are applied to avoid selection bias. Blinding is used to minimize performing bias and detection bias. However, methodological limitations still exist in the study. Due to the nature of acupuncture manipulation, the therapists and the participants cannot be blinded in this study. Therapists have to carry out the acupuncture manipulations and control the participant’s sensation of needling. In acupuncture trials, genuine double blinding is difficult to achieve, especially in countries with populations aware of acupuncture (Additional file 1).

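### The hypothesis claims acupuncture is at least as effective as mosapride, but no non-inferiority margin is defined and the planned two-sided difference test cannot support that claim

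*Protocol article*

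**What the plan says.** The Background of the protocol article closes with the trial's hypothesis: "Our hypothesis is that the effectiveness of acupuncture is no less than that of mosapride and better than routine health care". This is two pairwise claims, one of non-inferiority form (against mosapride) and one of superiority form (against routine care).

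Under Statistical analysis, the between-group method is "The Wilcoxon test or analysis of variance (ANOVA) will be used to compare the difference between groups", with the choice made by a Kolmogorov–Smirnov test. The error rate follows: "The statistical significance level will be set at 0.05 (two-sided) with a 95% confidence interval". No pair of arms is named there.

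The outcome is continuous: "The primary outcome measure will be the change in the weekly mean number of CSBMs over the 4 weeks of the intervention", and likewise over the follow-up. Allocation is "using a 1:1:1 ratio". The size is not derived from power: "For practical reasons, a sample size of 40 per group and a total number of 120 participants will be recruited". No margin appears in the hypothesis, sample size, outcome or analysis text. The article describes the trial as a pilot meant to give preliminary effects and effect sizes for later trials.

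**The concern.** A test of difference takes equality as its null hypothesis. Rejecting it shows that two arms differ. Failing to reject shows only that the data did not separate them. A claim that one treatment is no worse than another needs the reverse arrangement: a null hypothesis of being worse by at least a stated margin, and an interval or test that excludes it. Without a margin the mosapride claim has no criterion by which it could be met or refuted.

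This is more than detail that an article may leave to an analysis plan. The margin is part of what a non-inferiority hypothesis means, and here the article fixes a different kind of test next to it.

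At stake is the statement made about the active comparator. In a trial of this size a non-significant comparison with mosapride is likely even if acupuncture is moderately worse, and nothing in the text bars that result from being reported as support for the hypothesis.

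**Working it through.** **Inputs.** From the article: 40 per group, 1:1:1 allocation, continuous primary outcome, two-sided 0.05, 95% confidence interval. Not in the article: SD, expected effect, margin, power, dropout. Everything below is therefore in SD units, with true differences and margins as assumed ranges, normal data with equal variances, and all 40 per arm analysed.

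**1. The plan's own figure.** 3 × 40 = 120, as stated. There is no power calculation to reproduce.

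**2. Precision of one pairwise difference.** Standard error = √(2/40) = 0.2236 SD. Half-width of the 95% interval = t(0.975; 78 df) × 0.2236 = 1.991 × 0.2236 = 0.445 SD.

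**3. How often a real deficit goes undetected.** For a true deficit d against mosapride, the noncentrality is d/0.2236. The probability of a non-significant two-sided t-test at 0.05 with 78 df is:

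| True deficit (SD) | Noncentrality | Non-significant |
|---|---|---|
| 0.2 | 0.894 | 86% |
| 0.3 | 1.342 | 74% |
| 0.4 | 1.789 | 58% |
| 0.5 | 2.236 | 40% |

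The normal approximation Φ(1.96 − d/0.2236) gives 86%, 73%, 57% and 39%, so the choice of formula hardly matters.

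**4. What 40 per arm could show if a margin were set.** With the two treatments truly equal and the lower 95% limit compared with a margin M, power ≈ Φ(M/0.2236 − 1.96):

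| Margin (SD) | Power at 40 per arm |
|---|---|
| 0.2 | 14% |
| 0.3 | 27% |
| 0.4 | 43% |
| 0.5 | 61% |

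For 80% power the margin would have to be (1.96 + 0.8416) × 0.2236 = 0.63 SD. A margin can be added, but this sample would support only a wide one.

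**5. What an overall ANOVA would say about routine care.** Its noncentrality is 40 × Σ(μᵢ − μ̄)², with 2 and 117 df. Take means for acupuncture, mosapride and control, in SD.
- Hypothesis true, (0.5, 0.5, 0): the deviations are 1/6, 1/6 and −1/3, their squares sum to 1/6, and the noncentrality is 6.67.
- Hypothesis false, (0, 0.5, 0): the deviations are −1/6, 1/3 and −1/6, giving the same sum and the same 6.67.

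The probability of rejection is 62% in both cases. A significant overall F test would not by itself show that acupuncture beats routine care; the pairwise contrast is needed.

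**The case against.** The strongest reply is that this is a pilot. It claims no power, its size was set by what the hospital can recruit, and its purpose is to estimate effects for a later trial. The article never says that a non-significant result will be read as non-inferiority, and it plans 95% confidence intervals, from which a non-inferiority reading is possible once a margin exists. All of that stands. It means that the percentages in step 3 describe a misreading the text leaves open, not a rule it adopts, and it lowers the severity. It does not remove the mismatch: the hypothesis is stated outright, and the only criterion beside it is a two-sided significance level.

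Three stronger readings are tempting but not supported.

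- A reader might infer that the plan can answer neither half of the hypothesis. The article does not say that its only test is a three-group omnibus test. The Wilcoxon test is ordinarily a two-sample or paired procedure, so pairwise comparisons may be intended. A two-sided pairwise test with its 95% interval can support superiority over routine care. The gap there is only that the contrast is not named.
- A reader might infer an inflated family-wise error. That requires three pairwise tests with no gate, which the article does not state. The hypothesis names two contrasts, and for exactly three groups, pairwise tests run only after a significant ANOVA hold the level under a global null. A multiplicity rule may also sit in an analysis plan that is not shown.
- A reader might infer that the decision on a sham-controlled trial rests on the mosapride comparison. The Discussion says only "if acupuncture proves to be effective in this study, we will then compare acupuncture with a sham treatment" and does not mention mosapride in that condition.

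**Conclusion.** The point holds for the mosapride half of the hypothesis. As written, "the effectiveness of acupuncture is no less than that of mosapride" is a non-inferiority claim without a margin, placed beside a difference test that cannot establish it. The imprecision is material: the interval spans about ±0.445 SD, and assumed true deficits of 0.2 to 0.5 SD would pass as non-significant in about 86% to 40% of trials. These figures rest on the assumptions listed in the working; losses would widen the interval.

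For the routine-care half, the conclusion is limited to naming the contrast. The severity is should-fix: the pilot aim limits the consequence, but the correction changes what the trial may legitimately conclude about its active comparator.

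**What to change.** Choose one of two routes for the mosapride comparison.

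1. Keep the claim. State and justify a margin in CSBMs per week before any outcome data are examined, and judge acupuncture minus mosapride solely by whether the lower 95% confidence limit lies above minus that margin. Acknowledge the limited power shown above.
2. Drop the claim, which suits a pilot better. Remove the mosapride clause from the hypothesis, report the acupuncture–mosapride difference as an estimate with its 95% interval, and state that a non-significant p-value will not be interpreted as non-inferiority.

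Under either route, name acupuncture versus routine care in the Statistical analysis section as the pairwise superiority contrast, tested two-sided at 0.05 with its 95% interval.

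The cost is a few sentences in the Background and Statistical analysis sections. No extra patients or data are needed. The price is a more modest statement about mosapride.

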## Methods/design

### Study design

This is a prospective parallel-arm randomized controlled pilot trial comparing acupuncture with a pharmacological intervention (mosapride citrate) and usual care (control group). We will recruit patients who have sustained an ischemic stroke and present with constipation, according to predefined inclusion and exclusion criteria, between January 2017 and September 2019. Participants will be randomly allocated to one of three groups and will receive continuous treatment for 4 weeks. Repeat assessments will take place after treatment and later, at 8 weeks after inception. All participants will be asked to keep a defecation diary including weekly number of complete spontaneous bowel movements (CSBMs), SBMs, stool consistency, defecation difficulty, and laxative use and dosage, beginning at baseline during the 8-week assessment period. All outcomes will be assessed at baseline, and at 4- and 8-weeks after randomization, according to the defecation diary (Fig. 1).

**Fig. 1 Fig1:**
[figure not shown]
Trial flow chart

### Randomization and allocation concealment

Participants will be randomly assigned to one of three groups (the acupuncture group, the medication group, or the control group) using a 1:1:1 ratio. The generation and allocation of a random sequence for group assignment will be conducted by the Research Centre of Clinical Epidemiology, which is affiliated to Peking University Third Hospital in China. Individuals involved in participant randomization will be blinded and will not participate in the recruitment and inclusion of participants. The block randomization method (block size of 6) will be adopted to generate the random sequence, using the Statistical Analysis System (V.9.1.3; SAS Institute Inc., Cary, North Carolina, USA). Opaque computer-generated sealed envelopes will be produced for the randomization and allocation. The envelopes will be numbered consecutively with a serial number on the outside and will contain the allocation information. An envelope will be opened when a participant enters the study after the baseline measurements have been taken. Participants will be allocated to one of the three groups and receive an intervention according to their group allocation. The random allocation sequence and the opaque sealed envelopes will be kept separately by two specific researchers.

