### Blinding

Data managers (including the telephone interviewer during the follow-up period) and statisticians will be blinded to participant group assignment. Therapists, data managers, and statisticians will not be allowed to communicate with others about the participants’ allocation.

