#### Recruitment and baseline assessment

Researchers will recruit participants from outpatient clinics and inpatient wards of the acupuncture and moxibustion departments. Recruitment posters will be posted in the hospital. The posters will contain a brief, Institutional Review Board-approved introduction to the study, the participants, the interventions, and contact information for the researchers. The recruitment information will also be uploaded to the hospital website (http://www.bjzhongyi.com).

Consent will be obtained by one of the investigators, with a witness present. Following written informed consent, eligible patients will be asked to complete a general information form including name, gender, age, medical history, etc. and complete a 1-week defecation diary as the baseline assessment. A neurologist will determine the Glasgow Coma Scale score and the National Institute of Health Stroke Scale score for each participant and these scores will be used to decide whether to include the patient in the study according to the inclusion and exclusion criteria. Personal information about potential and enrolled participants will be collected and maintained confidentially.

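### A single fixed block size of 6 in a one-site, open-label trial leaves some upcoming allocations deducible, at most about one in five with certainty

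*Protocol article*

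**What the plan says.** The section on randomization and allocation concealment assigns participants "using a 1:1:1 ratio" and names one block size: "The block randomization method (block size of 6) will be adopted to generate the random sequence". It describes no variation in size.

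The same section sets out the safeguards. An outside epidemiology centre generates the sequence. The envelopes are opaque, sealed and consecutively numbered on the outside, and each is opened only after baseline measurement. Two different researchers hold the sequence and the envelopes. In addition, "Individuals involved in participant randomization will be blinded and will not participate in the recruitment and inclusion of participants".

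Under Blinding, data managers (including the follow-up telephone interviewer) are named as blinded, and "statisticians will be blinded to participant group assignment". A further rule applies to allocation: "Therapists, data managers, and statisticians will not be allowed to communicate with others" about it. Recruiters appear in neither list.

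On recruitment: "Researchers will recruit participants from outpatient clinics and inpatient wards of the acupuncture and moxibustion departments". These departments belong to one hospital. The Discussion concedes that "the therapists and the participants cannot be blinded in this study", yet it relies on randomization and concealment to prevent selection bias.

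**The concern.** A sealed envelope hides its own content. It does not hide what earlier envelopes contained once treatment has started. In this trial earlier allocations show: the treatment is open, and acupuncture patients attend 16 sessions over four weeks in the clinics and wards where recruitment goes on. With a constant block size, the serial number on the next envelope gives its position in the block, and the earlier allocations in that block limit what can follow.

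Anyone who puts the two together can bring forward, delay or withhold an enrolment according to the arm expected next. Eligibility runs from 2 weeks to 6 months after stroke, so timing can shift without breaching a criterion. The result would be arms that differ in prognosis. The trial is meant to supply effect sizes for later sample size calculations, so any such bias would be carried forward.

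**Working it through.** **Inputs.** Block size 6 and ratio 1:1:1 (Randomization and allocation concealment). Sample size: "a sample size of 40 per group and a total number of 120 participants will be recruited during the entire study" (Sample size). Recruitment from January 2017 to September 2019, which is 33 months (Study design). One-week baseline diary between consent and envelope opening (Recruitment and baseline assessment).

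**Consistency with the plan's own figure.** 120 / 6 = 20 complete blocks, and 20 × 2 = 40 per arm. This agrees with the stated 40 per group.

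**Predictability when the envelope is opened.** Assume an observer who knows the block size and every earlier allocation in the block. A block has 6! / (2! × 2! × 2!) = 90 equally likely orderings. Counting over all of them:

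| Position in block | Next arm certain | At least one arm ruled out | Acupuncture ruled out | Best guess correct |
|---|---|---|---|---|
| 1 | 0 | 0 | 0 | 0.333 |
| 2 | 0 | 0 | 0 | 0.400 |
| 3 | 0 | 0.20 | 0.067 | 0.500 |
| 4 | 0 | 0.60 | 0.200 | 0.533 |
| 5 | 0.20 | 1 | 0.400 | 0.600 |
| 6 | 1 | 1 | 0.667 | 1 |
| Mean | 0.200 | 0.467 | 0.222 | 0.561 |

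The fifth position is certain only when the last two places belong to the same arm: 3 × 6 = 18 of 90 orderings, or 0.20. Certain allocations per block are therefore 0.20 + 1 = 1.2, that is 1.2 / 6 = 20%, and over 20 blocks 24 of 120. At least one arm is ruled out for 2.8 × 20 = 56 of 120, and acupuncture in particular for 1.333 × 20 ≈ 27. The best guess is right 56.1% of the time, against 33.3% by chance.

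**Predictability at consent.** Assume even accrual, a lag of exactly one week, Poisson arrivals, and that allocations made during that week are unknown at consent.

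- 33 months is 33 × 52 / 12 = 143 weeks, so the rate is 120 / 143 ≈ 0.84 per week.
- Chance of no intervening allocation: exp(−0.84) ≈ 0.43. Chance of exactly one: 0.84 × 0.43 ≈ 0.36.
- With none, certainty is 0.20. With one unseen, only the sixth place can be certain, and only if the last two places are the same arm: 0.20 / 6 = 0.033. With two or more unseen, nothing is certain, because no arm has three places.
- Total: 0.43 × 0.20 + 0.36 × 0.033 ≈ 0.10, or about 12 of 120.

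**Effect of varying the block size.** Simulation of 200 trials of 120, with sizes equally likely and an observer who knows the set of sizes but not their order:

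| Sizes | Certain | Best guess correct |
|---|---|---|
| 6 only (exact) | 20% | 56% |
| 3, 6 | 8.6% | 58% |
| 6, 9 | 5.3% | 54% |
| 3, 6, 9 | 3.7% | 55% |
| 6, 9, 12 | 2.5% | 53% |

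**The case against.** The stated concealment is sound in most respects: outside generation, opaque serial envelopes, opening after baseline, split custody, and randomization staff who do not recruit. The ban on therapists discussing allocation acts directly on the most likely leak. A block of 6 is twice the number of arms, not the smallest possible. A neurologist scores the stroke scales that decide eligibility and a witness attends consent, both of which limit discretion. Withholding an envelope after the diary means dropping a consented patient who has baseline data. The trial is also a pilot.

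Much of this stands. It lowers the risk without closing the route, because the ban names neither recruiters nor participants and cannot hide who attends for needling.

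A reader might infer more than the text supports:

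- That recruiters do know the sequence. The article does not say that they treat patients, see every allocation or are told the block size. A condensed article may also leave out that the size is withheld from them.
- That 24 patients would in fact have a known allocation. That is a ceiling for perfect tracking at envelope opening.
- That the self-reported primary outcome makes the selection bias worse. Self-report in an open trial is a matter of measurement bias. Selective enrolment acts separately, through who enters each arm.
- That no analysis could help. Baseline bowel movements are recorded, so imbalance on them can be examined and adjusted for. Imbalance on unmeasured factors cannot.

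**Conclusion.** The point holds as a design weakness that is cheap to remove. Given one constant block size, consecutive numbering, open treatment, and recruitment and needling in the same departments, some upcoming allocations can be deduced from past ones, and no stated safeguard fully prevents it. The size is at most 20% known with certainty at envelope opening (expected 24 of 120), and about half that at consent under the accrual assumptions above. Both figures assume a recruiter who knows the block size and has seen every earlier allocation, except those made in the diary week for the consent figure. The finding does not depend on when the article appeared relative to enrolment.

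This is a risk of selection bias. The documents contain no evidence that it occurred, and they do not show that concealment has failed. They do make the Discussion's reliance on concealment to prevent selection bias stronger than the method supports.

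**What to change.** For any allocations not yet made, have the independent epidemiology centre generate the remaining sequence with block sizes drawn at random from multiples of three, for example 6 and 9, or 3, 6 and 9. Withhold the sizes from all recruiting and treating staff. State that recruiters are kept unaware of block sizes and of past allocations.

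The gain is mainly the removal of certainty, from 20% to roughly 4–5% with these sets. Best-guess accuracy stays near 54–55% if the set of sizes becomes known, so secrecy about the sizes matters as much as varying them.

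The cost is one new list, a new set of envelopes for the remaining serial numbers, and a small possible imbalance in final arm sizes. A block of 9 has three places per arm, so stopping inside it can separate two arms by at most 3. The documents do not show whether recruitment is still open. If it has closed, what remains is to qualify the Discussion's statement on selection bias.
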